## Trial outcomes

The primary outcome is energy intake in kcal at 9 months of age (visit window 9–11 months), as measured by multipass 24-hour dietary recall. Secondary and tertiary outcomes are defined in table 2.

**Table 2 T2:** Trial outcomes at 9 months of age (window 9–11 months)

Endpoint	Definition
Energy intake	Percentage of infants meeting daily energy requirements at 9 months of age (window 9–11 months), measured by multipass 24-hour dietary recall.
Protein, iron, zinc and folate intake	Percentage of infants meeting daily protein, iron, zinc and folate requirements at 9 months of age, measured by multipass 24-hour dietary recall.
Length-for-age Z-score	Length-for-age expressed as a Z-score compared with the WHO 2006 reference median
Weight-for-age Z score	Weight-for-age expressed as a Z-score compared with the WHO 2006 reference median
Weight-for-length Z score	Weight-for-length expressed as a Z-score compared with the WHO 2006 reference median
Haemoglobin	Concentration of haemoglobin (in g/dL) in a whole blood sample, measured by HemoCue point-of-care assay and adjusted for altitude
Microbiome maturity	Microbiota-for-age Z-score
Environmental enteric dysfunction	Biomarkers of intestinal inflammation (faecal neopterin and myeloperoxidase), small intestinal damage (plasma I-FABP and citrulline), intestinal permeability (faecal A1AT), microbial translocation (plasma sCD14, LBP), systemic inflammation (plasma CRP, AGP, TNF-alpha and K:T ratio) and growth hormone axis (IGF-1)
Innate immune cell phenotype	Surface marker expression by peripheral blood monocytes and neutrophils
Innate immune cell function	Surface marker expression and cytokine secretion from innate immune cells challenged with lipopolysaccharide in vitro relative to unstimulated controls Capacity of innate immune cells to internalise bacteria in vitro
Plasma essential amino acids	Plasma concentrations of phenylalanine, valine, threonine, tryptophan, methionine, leucine, isoleucine, lysine and histidine, as measured by LC-MS-MS
Plasma choline	Plasma concentration of choline, as measured by LC-MS-MS
Urinary metabolic signature	Global untargeted metabolomic phenotyping undertaken by ^1^H nuclear MR spectroscopy

AGP, alpha-1 acid glycoprotein; CRP, C reactive protein; LBP, lipopolysaccharide binding protein; LC-MS-MS, liquid chromatography-mass spectrometry.

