The primary outcome, percentage of infants meeting energy intake (kcal/day), will be calculated using measured intake data from dietary recalls from all participants. Dietary energy intake (DEI) was collected through an interactive, multiple-pass, 24-hour recall at the 9-month endpoint among all children, and in 50% of children through an additional dietary recall 7 days later. The DEI estimate will be used with a logistic regression model clustering for the repeat measure using the multilevel mixed-effects logistic regression method. This method will be implemented within STATA. It is well recognised that the dietary intake data contain a lot of uncertainty, and thus, we will conduct a sensitivity analysis using the National Cancer Institute (NCI) method calculated for usual overall average intake. We will estimate the mean and percentiles of usual energy intake distributions using the NCI method.^53 54^ This method adjusts for measurement error—primarily due to day-to-day variability in intakes—in observed, single-day estimates of nutrient intakes. We will use the NCI macros, DISTRIB and MIXTRAN, plus bootstrapped SEs for hypothesis testing.^25 27^ The MIXTRAN macro fits a mixed effects model of usual energy intake, and the DISTRIB macro uses a Monte Carlo procedure to estimate percentiles of the usual intake distribution. We will use the MIXTRAN macro to fit a model of energy intake with a fixed effect for intervention group and the DISTRIB macro to estimate usual energy intake distributions by treatment group. We will bootstrap the parameters to estimate the SE of the mean usual intakes. We will use the point estimates and SE estimates to construct 95% CIs and calculate p values for difference in mean by intervention group based on Welch’s t-test. Bootstrapped SEs will be calculated using bootstrap samples. When intake or the number of repeat recalls is low, it is common for the NCI method to fail to converge. In cases where convergence prohibits bootstrapping, we will test hypotheses using the Wilcoxon testing for clustered method.

We will also interpret the mean intake of each nutrient for the primary and secondary analysis in each arm and will present mean differences with the 95% CI for interpretation.

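### The sensitivity analysis for day-to-day recall variation tests mean usual intake, so the corrected percentage of infants meeting the energy requirement has no formal inference

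*Protocol article*

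**What the plan says.** The Statistical analysis section states: "The primary outcome, percentage of infants meeting energy intake (kcal/day), will be calculated using measured intake data from dietary recalls from all participants". Table 2 under Trial outcomes defines the energy endpoint the same way: "Percentage of infants meeting daily energy requirements at 9 months of age (window 9–11 months), measured by multipass 24-hour dietary recall". The Sample size section powers the trial on that proportion. The text above Table 2 differs: "The primary outcome is energy intake in kcal at 9 months of age (visit window 9–11 months), as measured by multipass 24-hour dietary recall".

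The main model is binary: "The DEI estimate will be used with a logistic regression model clustering for the repeat measure using the multilevel mixed-effects logistic regression method". Every child has one recall, with a repeat "in 50% of children through an additional dietary recall 7 days later".

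Because recall data are uncertain, the section adds an NCI-method sensitivity analysis aimed mainly at day-to-day variability. Its descriptive output is broad: "We will estimate the mean and percentiles of usual energy intake distributions using the NCI method", with distributions by treatment group from DISTRIB. The model is described as follows: "We will use the MIXTRAN macro to fit a model of energy intake with a fixed effect for intervention group". The inference is narrower. Bootstrap standard errors are for mean usual intake, and the section will then "calculate p values for difference in mean by intervention group" using Welch's t-test. If convergence rules out bootstrapping, the fallback is a clustered Wilcoxon test.

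**The concern.** A sensitivity analysis should re-examine the primary quantity under the departure that motivates it. Here the departure is day-to-day variation around a child's usual intake. If that variation is additive with mean zero, it widens the distribution of single-day intakes without moving its centre. The arm means, and the difference between them, are therefore unbiased with or without the correction. The share above a cut-off depends on the spread as well as the centre, so it is distorted.

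The stated test thus addresses a quantity that this error does not bias. The quantity that it does bias is left with description only, and the rank-based fallback does not address the percentage either. At stake are the adequacy percentages reported for each arm, which readers concerned with feeding policy are likely to quote.

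**Working it through.** **1. The plan's own figure.** Inputs from the Sample size section: 86 evaluable infants per arm, 65% meeting requirements in the IYCF arm, a 20% increase, two-sided 5%. Read as 65% against 85%, with pooled variance under the null:

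- null SE = √(2 × 0.75 × 0.25 / 86) = 0.0660
- alternative SE = √((0.65 × 0.35 + 0.85 × 0.15) / 86) = 0.0642
- power = Φ((0.20 − 1.96 × 0.0660) / 0.0642) = 86.4%

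This reproduces the stated 86%. A relative 20% increase (65% against 78%) would give 47.1%, so the figure means 20 percentage points. The powered quantity is a difference in the percentage meeting requirement.

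**2. Effect of day-to-day variation.** Let usual intake be normal with mean μ and between-child SD σ. Let a single day's intake be usual intake plus independent error with variance rσ², and let the cut-off be c.

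- single-day share at or above c: Φ((μ − c) / (σ√(1 + r)))
- usual-intake share at or above c: Φ((μ − c) / σ)
- hence usual share = Φ(z × √(1 + r)), where z is the normal quantile of the single-day share
- the difference between arm means does not involve r

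**3. Numbers.** z(0.65) = 0.385 and z(0.85) = 1.036. The documents do not give r, so a range is assumed.

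| Assumed r | IYCF, usual | IYCF-plus, usual | Difference | Shift in levels (points) |
|---|---|---|---|---|
| 0 (as observed) | 65.0% | 85.0% | 20.0 | – |
| 0.5 | 68.2% | 89.8% | 21.6 | 3.2 and 4.8 |
| 1 | 70.7% | 92.9% | 22.2 | 5.7 and 7.9 |
| 2 | 74.8% | 96.4% | 21.6 | 9.8 and 11.4 |

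**4. Scale.** With 86 per arm at 65% and 85%, the 95% half-width for the difference is 1.96 × 0.0642 = 12.6 points. A shift of about 2 points in the difference is small against that.

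**5. Can the planned percentiles fill the gap?** Only informally. No cut-off, SE, CI or test is attached to them. The Follow-up data collection section bases energy requirements on body weight in kilograms, so each infant has a separate threshold. Percentiles of intake in kcal cannot be read against a single value.

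**The case against.** Several points on the other side stand.

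- A reader might infer that the primary result goes unchecked. It does not: usual-intake percentiles and distributions by arm are planned. What is missing is inference on the corrected percentage.
- A reader might infer that agreement between the two analyses would say nothing. Under the model above (normal intake, common variance, fixed cut-off), equal means and equal percentages are the same null hypothesis. Agreement is therefore informative about the existence and direction of an effect. It does not validate the percentage levels.
- Under the kcal wording above Table 2, which fits the energy-intake primary outcome named in the abstract and Objective 1, a comparison of means is the matching analysis. The mismatch arises only under the percentage wording.
- Table 2 and the Sample size section define the percentage by 24-hour recall. The observed percentage therefore meets its own definition; it is biased only if read as adequacy of usual intake.
- For the same reason, a reader who took 65% and 85% as usual-intake proportions would infer a marked loss of effect: single-day differences of 17.8, 16.1 and 13.7 points at r = 0.5, 1 and 2. The Sample size section ties its target to recall, so the documents do not support that starting point.
- Welch's test treats the arm means as independent, although one fitted model supplies both. The effect on the p value is not quantified and may be small.

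Two defences are weaker. The mixed-effects logistic model handles correlation between repeat recalls, but its outcome is still whether one day's intake met requirement, and the section derives no usual-intake percentage from it. Nor is this only detail left to the statistical analysis plan, since the article itself states which quantity is bootstrapped and tested.

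**Conclusion.** The concern holds in a limited form. If the primary outcome is the percentage meeting requirement, as in the Statistical analysis section, Table 2 and the Sample size section, the stated NCI inference does not target it, and the corrected percentage has no CI or test. For an assumed variance ratio of 0.5 to 2, adequacy levels would move by 3 to 11 points and the arm difference by about 2. The benefit therefore lies mainly in the levels reported, and the randomised contrast changes little.

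These figures rest on normal intake, classical additive error, equal variances in the arms, one fixed cut-off and a variance ratio that the documents do not supply. Systematic recall error that differs by arm, which is possible in an open-label trial, would not be removed by either analysis. This is an inexpensive improvement and does not invalidate the planned primary analysis.

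**What to change.** 1. Reconcile the primary outcome wording: kcal in the Trial outcomes text, percentage in Table 2, Sample size and Statistical analysis.
2. If the percentage is primary, fit the NCI model to intake relative to each infant's requirement. Have DISTRIB output, by arm, the percentage with usual intake at or above requirement.
3. Obtain the CI and p value for the arm difference by bootstrapping the difference itself, resampling households with all their recalls and refitting the model each time.
4. Keep the difference in mean usual intake as a secondary output, also from a bootstrap of the difference instead of a Welch test on separate arm SEs.

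If kcal is primary, the mean comparison can stay as the sensitivity analysis, and the main model needs to be aligned with that outcome.

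The cost is one more output from macros already planned and some computing time. No new data are needed. Some bootstrap samples may fail to converge, a problem that the section already anticipates.

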## Laboratory analyses

Biological samples will be used to evaluate the nutrient profiles, EED, systemic inflammation, innate immune function, metabolic phenotype and the gut microbiota, as shown in table 6. This is a tertiary outcome being measured on everyone with samples available for baseline and endline. The study is not powered for this outcome and is exploratory.

**Table 6 T6:** Laboratory analyses

Sample type	Assay	Method	Location of work	Study subjects	Time-points
Plasma	I-FABP, CRP, AGP, TNFα, LBP, sCD14, IGF-1	ELISA	Zvitambo	All	Baseline, endline
Peripheral blood leucocytes	Innate immune cell phenotype*	Flow cytometry	Zvitambo	All	Baseline, endline
Whole blood	Whole Blood Culture with and without LPS	Cell culture, flow cytometry and ELISA	Zvitambo	All	Baseline, endline
Whole blood	Bacterial binding Assay	Cell culture, flow cytometry	Zvitambo	All	Baseline, endline
Stool	Myeloperoxidase, neopterin, alpha-1 antitrypsin	ELISA	Zvitambo	All	Baseline, endline
Urine	Global untargeted metabolomic phenotyping	^1^H NMR spectroscopy	Southampton, UK	All	Baseline, endline
Plasma	Global untargeted metabolomic phenotyping	^1^H NMR spectroscopy	Southampton, UK	All	Baseline, endline
Plasma	Kynurenine:tryptophan ratio, citrulline, essential amino acids, choline	Ultrahigh-performance liquid chromatography tandem mass spectrometry with electrospray ionisation	Southampton, UK	All	Baseline, endline
Stool	Whole metagenome shotgun sequencing	Illumina HiSeq	Blizard Institute, UK	All	Baseline, endline
Stool	Metabolic phenotyping of faecal water	^1^H NMR spectroscopy	Southampton, UK	All	Baseline, endline
Urine	Aflatoxin M1 and creatinine	ELISA	Zvitambo	All	Baseline, endline

*Expression of surface activation markers HLA-DR, CD64 and CD16 on monocytes and HLA-DR, CD64, CD16 and CD62L on neutrophils.

AGP, alpha-1 acid glycoprotein; CRP, C reactive protein; I-FABP, intestinal fatty acid binding protein; IGF-1, insulin like growth factor 1; LBP, lipopolysaccharide binding protein; LPS, lipopolysaccharide; NMR, nuclear MR.

### EED and systemic inflammation

We will use a combination of plasma and stool ELISA assays to compare the impact of IYCF and IYCF-plus on EED, by characterising the hypothesised causal pathway from the gut to growth, measuring markers of intestinal inflammation (stool myeloperoxidase, neopterin) small intestinal damage (plasma I-FABP), intestinal permeability (alpha-1 antitrypsin), microbial translocation from the gut (plasma LBP, sCD14), systemic inflammation (AGP, C reactive protein, TNFα) and growth hormone activity (plasma IGF-1). We will also measure aflatoxin M1 in urine, to assess recent exposure to dietary aflatoxin, which is a plausible cause of EED and may be reduced in the IYCF-plus arm since PVA maize appears less prone to fungal contamination.

### Immune function

Immune cell activation is metabolically costly and chronic activation by recurrent infections/EED may create a barrier to children meeting their nutrient requirements by: (1) driving inflammation and oxidative stress, (2) contributing to enteropathy and (3) compromising the capacity of innate immune cells to defend against new infections, which further deplete dietary nutrients. Multiple innate and adaptive immune mediators are dysregulated in undernourished children,^55^ but little is known about if/how nutritional interventions affect immune defences.^56^ We will use whole blood samples to compare innate immune cell phenotype and function between randomised groups. We will quantify surface expression of activation markers HLA-DR, CD64 and CD16 on blood monocytes, and CD64 and CD62L on blood monocytes and neutrophils via flow cytometry. To characterise the functional capacity of innate immune cells to respond to pathogen challenge, we will quantify proinflammatory cytokine secretion in supernatants derived from whole blood cultures with and without bacterial lipopolysaccharide. Whole blood culture with and without fluorescent-labelled *Escherichia coli*-coated bioparticles will be used to quantify uptake of bacteria via flow cytometry.

### Metabolic phenotyping

A targeted ultra-performance liquid chromatography-mass spectrometry-based assay will be used to measure tryptophan-related metabolites in plasma (funding permitting).^57^ This includes metabolites involved in the kynurenine, serotonin and indole pathways. In addition, downstream NAD+ related metabolites, such as nicotinic acid, nicotinamide and nicotinamide riboside will be measured together with markers of systemic inflammation (neopterin), enterocyte mass (citrulline) and the neurotransmitter dopamine. ^1^H nuclear MR spectroscopy will be used to characterise the metabolic profiles of urine, plasma and faecal water samples. This approach measures H-containing metabolites present above the limit of detection in the samples in an untargeted manner. This captures information on amino acids, gut microbial metabolites and metabolites involved in choline and energy metabolism. It may also be used to study dietary components and assess variation in their digestion.

### Microbiome sequencing

Whole metagenome shotgun sequencing will be employed on stool samples to examine the effect of the trial interventions on the gut microbiome and its association with growth. DNA will be extracted from stool aliquots (200 mg) using the Qiagen PowerFecal Pro DNA kit, followed by metagenomic sequencing library preparation. Following qualitative and quantitative assessment of sequencing libraries, sequencing will be performed via the HiSeq 2500 platform producing 6–10 million sequencing reads per sample. Following quality control and trimming of human reads, sequencing reads will be processed through validated pipelines to generate compositional (MetaPhlAn V.3) and functional (HUMAnN V.3) readouts of the gut microbiome. Microbiome maturity will be assessed as previously described using a control dataset generated from the SHINE trial.^58^ Aliquots of stool stored in glycerol will be used to isolate microorganisms of interest for downstream experiments assessing the influence of the gut microbiome on EED and growth.

## Qualitative studies

The first qualitative substudy will develop a more in-depth understanding of how the CHAIN interventions were integrated into household nutrition practices, and the cultural, economic and social processes that shape this. Up to 20 families were purposively sampled based on type of household, caregiver characteristics and trial arm. Semistructured interviews were conducted to explore a range of themes, including any changes in the participants’ receptiveness to the food supplements or children’s response to them, the ability to maintain compliance with the food preparation guidelines, and challenges they may have experienced (eg, accessing or storing the food supplements). The interviews also focus on relevant cultural, economic and social processes operating at the household level that may influence food preparation and consumption practices and explore how these shape the sustainability of the intervention. Additionally, emphasis was placed on exploring the role that household and area-level gender dynamics may play in decision-making practices.

A second qualitative substudy will identify the ways in which household migration (defined here as people who have moved away from a household for 3 months or more) influences food security. Thirty participating households were identified from the baseline survey as having at least one family member who has migrated across a range of geographical scales (local, regional, national and international) and where possible representing different household types (including, male-headed or female-headed households, orphan-headed households, elder-headed households). In-depth interviews were conducted with study participants to explore the interactions that exist between household migration and remittance practices (receiving and sending) and their potential to influence household food consumption and production practices. In addition, the in-depth interviews aim to consider the importance of geographical scale to remitting practices and their influence on food consumption and production and investigate possible interactions between migration and household participation in the CHAIN interventions.

Interviews and focus groups were audio recorded, for subsequent transcription and translation; transcripts will be entered into NVivo for coding, analysis and interpretation. Analysis will proceed using both deductive and inductive approaches and will use the framework method often employed in multidisciplinary health-related research. All audio recordings will be destroyed, although transcriptions will be stored securely and made available for future analysis as required.

## Trial risks and adverse events

All interventions are commercially available foods (beans, egg powder, moringa, maize) or food supplements that are widely used globally (SQ-LNS). Peanuts and eggs are both staple foods in rural Zimbabwe; although both are potentially allergenic among infants in high-income settings, the prevalence of food allergies in sub-Saharan Africa is extremely low.^5 59 60^ SQ-LNS, which contains peanuts, was used in the same community in the SHINE trial among more than 2000 infants. From over 365 000 doses of SQ-LNS that were given to infants in SHINE, there were no allergic reactions and no serious adverse events.^5^ Only two adverse events were possibly or probably related to SQ-LNS; both resolved without sequelae.^5^ Children with a known allergy to peanuts or eggs will be excluded from the study to further minimise the risk of adverse events. All adverse events will be reported and reviewed by the study physician, and a tabulated monthly summary will be sent to an independent safety monitor. All serious adverse events and trial-related adverse events will be reported to the Medical Research Council of Zimbabwe according to established time frames.

The COVID-19 pandemic poses a potential risk to research activities in the community. We ensured that research staff wear personal protective equipment and practice physical distancing to keep themselves and research participants safe. All staff were trained in COVID-19 protocols. Interviews were conducted in a confidential outdoor part of the homestead wherever possible. CHWs conduct their activities with guidance for safe working from the Ministry of Health and Child Care. Procedures were reviewed as the pandemic progresses, and any changes discussed with the District Health Executive and with the Medical Research Council of Zimbabwe. The food supplements are stopped at 12–15 months and not continued after the trial.

